## Monitoring Plan

Assessment of the availability (collection and proper shipment/storage) of the compartmental samples (and of blood viral loads) will be conducted periodically. Also, study accrual and follow-up will be assessed (overall, by gender, and by antiretroviral-naïve versus antiretroviral-experienced subjects).

## Analysis Plan

Because the men and women in this study may have different viral load levels, especially in genital secretions, gender-specific cutpoints may be used in the analysis. Sample size permitting, the influence of subjects’ baseline antiretroviral-naïve (< 1 week) versus antiretroviral-experienced status will be examined. In addition to the time-to-event analyses described below, interval-censored analysis methods will be used.

Baseline blood plasma viral load will be the average of the preentry and entry log10 HIV-1 RNA values.

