###### SCHEMA

VIROLOGIC STUDIES IN COMPARTMENTAL SAMPLES

FROM HIV-INFECTED SUBJECTS CHANGING OR INITIATING

POTENT ANTIRETROVIRAL THERAPY

DESIGN: A multicenter, cross-sectional, and longitudinal study designed to characterize differences in viral load and virus genotype and to assess the association between viral load and viral characteristics in blood (plasma and PBMCs) and nonblood compartments (saliva,genital secretions, and lymphoid tissues).

SAMPLE SIZE: 164 subjects.

POPULATION:  HIV-1-infected male and female subjects > 13 years of age initiating or changing potent antiretroviral therapy.

 Plasma HIV-1 RNA > 2000 copies/mL.

 Willing to contribute samples of blood, saliva, and either genital secretions or lymph tissues, or both.

NOTE: No antiretroviral drugs will be provided by A5077.

NOTE: Potent antiretroviral therapy is defined as a minimum of three antiretroviral drugs that includes any of the following combinations:

- two nucleoside analogues and a non-nucleoside reverse transcriptase inhibitor (NNRTI);
- two nucleoside analogues and abacavir;
- two nucleoside analogues and a protease inhibitor;
- two protease inhibitors and an NNRTI;
- two protease inhibitors and a nucleoside analogue; or
- a nucleoside analogue, an NNRTI, and a protease inhibitor.

STRATIFICATION: Subjects will be stratified by sex to ensure equal (50%) enrollment of males (n = 82) and females (n = 82).

DURATION: Subjects will participate in this study for 96 weeks.

SCHEMA, (Cont.)

OBJECTIVES:

Primary: 1. Evaluatethe relationship between baseline viral load in blood and in nonblood compartments and the time to virologic failure.

2. Evaluatethe relationship between viral load in nonblood compartments at the time of suppression of plasma HIV-1 RNA levels and the time to subsequentvirologic failure.

3. Analyze the frequency of detecting HIV-1 in saliva, genital secretions, and lymphoid tissues from subjects with persistently suppressed plasma HIV-1 RNA levels.

Secondary: 1. Investigate whether loss of HIV-1 suppressionoccurs earlier in blood or in nonblood compartments in subjects who have previously achieved viral suppression in blood and nonblood compartments.

2. Investigate whether HIV-1-drug-resistant mutations not present at baseline are acquired earlier in blood or in nonblood compartments.

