## Sample Size and Accrual

7.31 Virologic Failure

To minimize the assumptions needed to estimate power for the first primary objective, we consider virologic failure as a binary endpoint (yes/no) and model the probability of virologic failure as a function of baseline blood plasma viral load and a nonblood viral load measure. Blood viral load and nonblood viral load are considered to have a bivariate normal distribution with correlation = 0.4 (as observed in ACTG 347 between blood plasma and seminal plasma viral load). The nonblood viral load is dichotomized at its mean, while blood viral load is modeled as a continuous predictor on the log10 scale, with mean = 4.477 log10 copies/mL (30,000 copies/mL) and SD = 0.7 (as observed in ACTG 175).

Power is determined by logistic regression simulations with a two-sided alpha = 0.05, where the effect of the nonblood viral load is evaluated in a model that already contains blood viral load. The rate of virologic failure for a subject with mean levels of the viral load measures is assumed to be 30%. For each log10 higher baseline blood viral load, the odds ratio (OR) for virologic failure is assumed to be 3 (approximately the OR observed in ACTG 364).

With 164 subjects enrolled, it is anticipated that baseline blood and nonblood viral loads will be available for 130 subjects (i.e., a 21% adjustment is made for the possibility of unavailable baseline measures). Then, there is 82% power to detect OR = 3.5, comparing subjects with high nonblood viral loads versus low nonblood viral loads in terms of virologic failure. This corresponds to a probability of virologic failure of 44% for a subject with high nonblood viral load compared with a probability of 19% for a subject with low nonblood viral load, both subjects having similar blood viral loads.

Similarly, there is 72% power to detect an OR = 3; this corresponds to virologic failure probabilities of 43% versus 20% for subjects having high and low nonblood viral loads, respectively.

Note that these power statements can be considered conservative, in that higher power is expected if the nonblood viral load is modeled as a continuous variable or if time-to-event methods are used instead of the binary, logistic regression approach used for the power calculations (and more so if the virologic failure rate is higher).

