7.51 Virologic Failure

The significance of baseline nonblood viral load in predicting subsequent virologic failure will be evaluated with Kaplan-Meier curves and in a Cox regression model that already includes a term for baseline blood viral load. A supplemental analysis will be performed in which subjects without blood viral load measures at week 16 or later will be considered censored in the analysis.

Subjects analyzed will be those with both a baseline blood plasma viral load and a baseline nonblood viral load.

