1.0 FEMALE SUBJECTS

1.1 Specimen Collection

The subject must refrain from any kind of sexual activity, douching, and inserting any intravaginal products for at least 48 hours prior to the collection of vaginal/cervical specimens. Samples will be collected by the following methods in the following order: Sno-Strip™, cervicovaginal lavage (CVL), cytobrush, and only for subjects coenrolled in A5029, a Pap smear will also be performed.

1.11 Endocervical canal fluid collected by Sno-Strip wicking. The purpose of this collection procedure is to obtain endocervical canal fluid for viral RNA quantification.

1. Gently insert an unlubricated speculum into the vagina.

2. Sno-Strips will be used as wicks to collect primarily cell-free virions from the endocervical fluid. If excess mucus or menses clot has accumulated near the cervical os, a large cotton-tipped cotton swab may be used to gently remove this material before inserting the Sno-Strips™.

3. Using forceps (ring or sponge forceps work well), gently insert three Sno-Strips simultaneously into the vagina, place through the cervical os into the distal endocervical canal, and hold in place to adsorb sample. Each Sno-Strip adsorbs approximately 8-µL of specimen. Adsorption usually takes approximately one minute, but may take a littlelonger.

4. Hold the narrow end of the three strips over and slightly inside one labeled plastic transport tube (1.5-mL cryovial) containing 500 µL of NASBA lysis buffer (provided by the University of North Carolina Retrovirology Laboratory). Cut the strips at the junction of the shoulder and neck of the Sno-Strip with scissors, allowing the narrow end to fall into the cryovial tube buffer.

5. Send the sealed vial to the local laboratory for processing.

1.12 Ectocervicovaginal lavage. The purpose of this collection procedure is to obtain a washing of virus and cells from the ectocervix and fluid from the posterior vaginal fornix for viral and immunologic studies.

1. Collect the ectocervicovaginal lavage by placing 10 mLof either normal saline or phosphate buffered saline in a 10-mL Luer-Lok® syringe.

2. Cut a sterile plastic transfer pipette just below the bulb, throw the bulb away and place the pipette tip on the syringe. Alternatively, a 14-gauge angiocath can be inserted over the tip of a 10-mL syringe. It may be helpful to seal the junction with parafilm.

3. Introduce the syringe through the speculum at the opening of the cervical os, but do not insert into os.

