2.3 Analysis

Virologic studies planned include the following:

- Quantitation of HIV-1 RNA levels in seminal plasma using the UltraSensitive Roche assay.
- Genotypic resistance studies (analysis of HIV-1 reverse transcriptase and protease sequences) in seminal plasma. NOTE: DNA extracted from seminal cells will be used for genotypic resistance studies when HIV-1 RNA levels in seminal plasma are low
  (< 1000 HIV RNA copies/mL).
- Detection and quantitation of HIV-1 proviral DNA (total and 2-LTR circles) in seminal cells using an in-house assay.

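### For genital secretions, sex-specific cutpoints are only permitted, and the analyses for objectives 1 and 2 name no sex term or stratum, although the male and female specimens are on different scales.

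*Protocol*

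**What the plan says.** The opening of Protocol section 7.5 states that, because men and women in the study "may have different viral load levels, especially in genital secretions, gender-specific cutpoints may be used in the analysis". The next sentence says that the influence of antiretroviral-naive versus experienced status will be examined if sample size permits.

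For objective 1, section 7.51 tests baseline nonblood viral load with Kaplan-Meier curves and "in a Cox regression model that already includes a term for baseline blood viral load". No other covariate is named. For objective 2, section 7.52 names Kaplan-Meier curves and a log-rank test, with no stratum. For objective 3, sections 7.33 and 7.53 commit to analysing genital secretions separately in men and women.

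The Schema makes sex the enrolment stratum: "Subjects will be stratified by sex to ensure equal (50%) enrollment", 82 of each.

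Appendix IV describes the specimens. In women, section 1.11 tells the clinician to "gently insert three Sno-Strips simultaneously into the vagina". Each strip takes up roughly 8 microlitres, and all three go into one vial holding 500 microlitres of lysis buffer. In men, section 2.3 plans "Quantitation of HIV-1 RNA levels in seminal plasma using the UltraSensitive Roche assay", and section 2.2 describes no dilution of that plasma. No common reporting unit or dilution correction is given.

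**The concern.** The protocol identifies the problem and makes a firm commitment for objective 3, but leaves the same specimens open for objectives 1 and 2. If one cutpoint is applied to two differently scaled measurements, the high and low groups partly sort subjects by sex. Two things follow. A real within-sex association is diluted, because many subjects who are high or low for their own sex are misclassified. And any sex difference in virologic failure is credited in part to the compartment, because neither analysis names sex. Unless the SAP settles it, the choice between common and sex-specific cutpoints also stays open until the data are seen.

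**Working it through.** **Inputs from Protocol 7.31.** "Power is determined by logistic regression simulations with a two-sided alpha = 0.05". The analysable number is 130 of 164: "it is anticipated that baseline blood and nonblood viral loads will be available for 130 subjects". Blood viral load has mean 4.477 and SD 0.7 log10. Its correlation with nonblood load is 0.4. The odds ratio per log10 of blood viral load is 3. The failure rate at mean levels is 30%. Nonblood load is split at a single mean, from one distribution for both sexes.

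**Step 1: reproduce the plan's power.** The model is logit(p) = log(0.3/0.7) + log(3) × (blood − 4.477) + log(OR) × (H − 0.5), where H = 1 for high nonblood load.
- At OR 3.5 and mean blood load this gives failure probabilities of 44.5% and 18.6% (plan: 44% and 19%). At OR 3 it gives 42.6% and 19.8% (plan: 43% and 20%).
- The plan states that "there is 82% power to detect OR = 3.5, comparing subjects with high nonblood viral loads versus low nonblood viral loads". Simulation gives about 84%. At OR 3 it gives about 74%, against a stated 72%. A 1,000-replicate simulation has a standard error of 1.2 to 1.4 points, so the stated figures are sound for one common distribution.

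**Step 2: the scale gap.**
- Fluid collected: 3 × 8 = 24 microlitres.
- Dilution: (500 + 24)/24 = 21.8-fold; log10(21.8) = 1.34.
- If results are not corrected, women's values are shifted by 1.34 log10 from this source alone.
- If they are corrected, a 50 copies/mL limit becomes 50 × 21.8 = about 1,090 copies/mL of cervical fluid, so the detection floors differ instead.
- The nonblood SD is not given. At an assumed 0.7, 1.0 or 1.2 log10, the shift is 1.9, 1.3 or 1.1 SD.

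**Step 3: add a sex offset to the Step 1 model** (n = 130, half women, true within-sex OR 3.5, no sex effect on failure). Power:

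| Assumed offset | Common cutpoint, no sex term | Common cutpoint, sex term | Sex-specific cutpoint, sex term |
|---|---|---|---|
| 0.7 SD | 54–56% | 58–59% | 77–84% |
| 1.34 SD | 27% | 35–36% | 77–84% |

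The range in the last column depends on where the true step lies. It is about 84% if the step coincides with the cutpoint used, and about 77% if the step is at the population mean while the cutpoint is estimated from each sex's sample. At the 1.9 and 1.1 SD offsets of Step 2, power with a common cutpoint and no sex term is 14% and 35%.

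**Step 4: type I error**, true nonblood OR 1, common cutpoint, no sex term:

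| Assumed offset | Sex OR for failure 1.5 | Sex OR for failure 2 |
|---|---|---|
| 0.7 SD | 6–7% | 8% |
| 1.34 SD | 8–9% | 14–15% |

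With a sex term it returns to about 5%. A sex term therefore cures the confounding but recovers little of the lost power; the sex-specific cutpoint is needed for that.

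**Step 5: cost of adjustment.** With neither factor related to outcome, power at OR 3.5 is 83.5% after adjusting for both sex and antiretroviral status, against 84.0% without.

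**The case against.** **A common cutpoint is not prescribed.** The single mean in 7.31 belongs to the power calculation, and the only analysis cutpoints mentioned in 7.5 are sex-specific. This stands: the figures above describe one permitted analysis, not a fixed rule. With nonblood load continuous, a graded effect and no sex term, power is about 87% (0.7 SD) and 75% (1.34 SD), against about 91% with a sex term. If the effect is truly a step, continuous modelling gives 56% and 46%, against about 62–63%.

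**Covariates belong in the SAP.** Section 7.51 names a minimum term, not a closed list. That is fair, but here the protocol raises the issue itself and settles it only as an option.

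**The offset is assumed.** Appendix IV gives no reporting unit or assay input volume for the female specimen. This stands, hence the ranges.

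**The fix is not a full cure.** Sex-specific cutpoints cannot remove a difference in detection floors. If 70% of women were below the floor (from the 30% lower bound of detection in section 1.1), power with sex-specific cutpoints falls from about 77% to about 66%. For objective 2, sized on detectable versus undetectable virus, the stratified test does most of the work.

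Stronger readings that a reader might infer are not supported:
- *High genital load largely means male.* Section 7.33 reports higher detection in women under suppression, and 7.32 cites 26% and 9% of women against 6% of men. Even with men offset upwards by 0.7 to 1.34 SD, a common mean cut makes the high group about 64–75% male.
- *Treatment history is ignored.* Section 7.5 says it will be examined if sample size permits. That caution is reasonable for objective 2: two of the scenarios in 7.32 with a 5% reference rate imply only 90 × 5% + 10 × 44% = 8.9 to 60 × 5% + 40 × 26% = 13.4 failures.
- *Every compartment is affected.* Nothing similar by sex is documented for saliva or lymphoid tissue.
- *The stated power is wrong.* It reproduces.

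**Conclusion.** The point holds for genital secretions under objectives 1 and 2. The plan recognises a sex difference, permits but does not require the remedy, and names no sex term or stratum, while its own appendix puts the male and female measurements on different scales. If a common cutpoint were used, the power loss at OR 3.5 would be about 20 to 30 points at an offset of 0.7 SD and 50 to 57 points at 1.34 SD, with type I error of about 6–15% if sex also affects failure.

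These sizes rest on an assumed offset, an assumed nonblood SD, an assumed sex odds ratio of 1.5 to 2, and the plan's logistic approximation in place of the Cox model. They also use all 130 subjects, although genital sampling is optional and the genital analysis would be smaller. The direction of the offset is uncertain, but an offset either way dilutes and confounds. The study calls itself exploratory and no stated figure is wrong, so this is an inexpensive improvement rather than an error that undermines the design.

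**What to change.** In Protocol 7.5, make sex-specific cutpoints for genital secretions a requirement by changing may to will. Stratify the genital-secretion Cox model in 7.51 and the genital-secretion log-rank test in 7.52 by sex. Saliva and lymphoid tissue need no change on this ground.

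As an optional, secondary step, name naive versus experienced status as a covariate in the objective 1 Cox model.

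The cost is wording only. Sex and treatment history are already collected, and adjusting for both costs about half a point of power when neither matters.

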7.51 Virologic Failure

The significance of baseline nonblood viral load in predicting subsequent virologic failure will be evaluated with Kaplan-Meier curves and in a Cox regression model that already includes a term for baseline blood viral load. A supplemental analysis will be performed in which subjects without blood viral load measures at week 16 or later will be considered censored in the analysis.

Subjects analyzed will be those with both a baseline blood plasma viral load and a baseline nonblood viral load.

7.52 Conditional Virologic Failure

The significance of nonblood viral load at the time of blood plasma viral suppression in predicting subsequent blood plasma virologic failure will be evaluated with Kaplan-Meier curves and the log-rank test. Additional analyses using the Cox regression model may also be conducted.

Subjects analyzed will be those with a week 16 nonblood viral load, with blood plasma HIV-1 RNA < 200 copies/mL at week 16 and a subsequent blood plasma viral load measure.

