A5077 is designed to analyze relationships between viral load in blood and nonblood compartments and time to virologic failure in subjects initiating or changing potent antiretroviral therapy. The virologic analyses in blood and nonblood compartments that are planned as part of this protocol might help to better segregate subjects with suppressed plasma HIV-1 RNA levels and identify those subjects who will subsequentlydevelop virologic failure. Of particular interest are cross-sectional and longitudinal analyses of blood and nonblood compartmental samples obtained from subjects at the following time points: 1) at study entry (baseline); 2) at the time of virologic suppression in plasma (< 200 HIV-1 RNA copies/mL); 3) at the time of virologic failure (HIV-1 RNA levels > 200 copies/mL); and 4) during follow-up. Characterization of the viral burden (HIV-1 RNA, proviral DNA) and other characteristics of the virus (genotypic resistance patterns, viral evolution, synctium-inducing/nonsynctium-inducing (SI/NSI), fitness, etc.) in blood and in specimens from nonblood compartments collected at these time points will contribute to the understanding of the virologic factors influencing the long-term effects of potentantiretroviral therapy.

A5077 includes sampling of lymphoid tissues from study participants because lymphoid organs constitute a major HIV-1 reservoir and are primary sites for HIV-1 replication (7,8). By using in situ hybridization and other quantitative methodologies, it has been possible to characterize and quantitate the different pools of HIV-1 in the lymphoid organs of infected individuals (7-9). Quantitative virologic studies in lymphoid tissue specimens obtained from antiretroviral-naïve individuals have shown that potent antiretroviral therapy that reduces plasma HIV-1 RNA to undetectable levels is also associated with significant reductions in the amount of HIV-1 in lymphoid tissues (10,11). These reductions in tissue viral burden are the consequence of a decline in the follicular dendritic cell (FDC)-associated virus together with a reduction of HIV-1 mRNA expression and proviral HIV-1 DNA in tissue CD4+ mononuclear cells. Despite these reductions, HIV-1 is still present in lymphoid tissues of individuals with suppressed plasma HIV-1 RNA levels (10).

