7.32 Conditional Virologic Failure

It is assumed that 61% of the enrolled subjects will be on study, have a week 16 nonblood viral load measurement, have blood plasma HIV-1 RNA < 200 copies/mL at week 16, and haveat least one subsequent blood plasma viral load measure, implying a sample size of 100 for the analysis of the second primary objective. The proportion of these subjects with detectable nonblood viral load is expected to depend on the compartment of interest and also on the assay method.

Kovacs et al. (45)reported that 26% of women with blood plasma HIV-1 RNA < 500 copies/mL had detectable HIV-1 in the genital tract. It was observed in ACTG 320/866 that out of 11 (9 at week 24 and 2 at week 40) paired on-treatment blood plasma and female genital tract specimens in which blood plasma HIV-1 RNA was undetectable (< 400 copies/mL by NucliSens), 9% (one) had detectable HIV-1 RNA in the genital tract (> 400 copies/mL by NucliSens). It was observed in ACTG 347/850 that 6% (one) of 17 men with undetectable blood plasma HIV-1 RNA (< 400 copies/mL by NucliSens) at week 16 had detectable seminal plasma viral load (HIV-1 RNA > 400 copies/mL by NucliSens). Dornadula et al. (5)reported that 45% (10) of 22 subjects (20 men and 2 women) with blood plasma HIV-1 RNA < 50 copies/mL had detectable viral HIV-1RNA levels in genital fluids. Hence, power statements for the second primary objective are given for a variety of scenarios. As above, virologic failure is considered as a binary endpoint.

If 40% of these 100 subjects have detectable nonblood viral load, then there is 80% power to compare subsequent blood plasma virologic failure rates of 5% versus 26% (similarly 80% power for 10% versus 34% and for 15% versus 42%), comparing subjects with low versus high levels of a nonblood viral load measure at the time of suppressed blood viral load. If 20% of these 100 subjects have detectable nonblood viral load, then there is 80% power to compare subsequent blood plasma virologic failure rates of 5% versus 33% (similarly 80% power for 10% versus 41% and for 15% versus 49%).

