If 10% of these 100 subjects have detectable nonblood viral load, then there is 80% power to compare subsequent blood plasma virologic failure rates of 5% versus 44% (similarly 80% power for 10% versus 53% and for 15% versus 62%). This is based on a two-tailed Fisher exact test, alpha = 0.05. Note that these power statements can be considered conservative, in that higher power is expected if the nonblood viral load can be modeled as a continuous variable (when it is detectable), or if time-to-event methods are used instead of the comparison of proportions (and more so if the virologic failure rate is higher).

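### Objective 2 is committed only to an unadjusted log-rank test, so a significant result cannot show that week 16 nonblood virus predicts failure beyond baseline blood viral load

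*Protocol*

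**What the plan says.** Protocol 7.52 states that the significance of nonblood viral load at the time of plasma suppression, as a predictor of later plasma failure, "will be evaluated with Kaplan-Meier curves and the log-rank test. Additional analyses using the Cox regression model may also be conducted". The log-rank test is the only test to which the protocol commits for this primary objective. The analysis set is subjects with a week 16 nonblood measurement, "with blood plasma HIV-1 RNA < 200 copies/mL at week 16 and a subsequent blood plasma viral load measure".

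Protocol 7.51, for the first primary objective, evaluates baseline nonblood viral load "in a Cox regression model that already includes a term for baseline blood viral load". The matching power calculation in 7.31 is built the same way and assumes: "For each log10 higher baseline blood viral load, the odds ratio (OR) for virologic failure is assumed to be 3". It also assumes a blood-nonblood correlation of 0.4 and an SD of 0.7 log10 for blood viral load.

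The Background and Rationale gives the purpose: the compartment analyses "might help to better segregate subjects with suppressed plasma HIV-1 RNA levels and identify those subjects who will subsequentlydevelop virologic failure".

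**The concern.** Two parallel primary objectives ask whether nonblood virus predicts plasma failure. One analysis accounts for blood viral load and the other does not. The protocol gives no reason for the difference.

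On the protocol's own figures, baseline blood viral load is related both to failure and to nonblood viral load, which is what a confounder needs. The Background also says that genital tract levels correlate with plasma levels. Subjects with detectable nonblood virus at week 16 may simply be those who started with higher plasma viral load. They would then fail more often even if nonblood virus carried no information of its own.

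At stake is the reading of a positive result. Nonblood specimens are harder to obtain than blood, and some need biopsy. Their use for sorting suppressed subjects depends on whether they tell more than a baseline plasma value that every analysed subject should already have.

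**Working it through.** **1. The plan's own figure.** Section 7.32 assumes 61% of 164 subjects, "implying a sample size of 100 for the analysis of the second primary objective" (0.61 × 164 = 100.04). With 40% detectable, the groups are 60 and 40, and the protocol states that "there is 80% power to compare subsequent blood plasma virologic failure rates of 5% versus 26" per cent. On method it says: "This is based on a two-tailed Fisher exact test, alpha = 0.05". Exact enumeration of that test gives 81.9%, so the 80% is reproduced. The calculation is unadjusted, like the log-rank test. The expected number of failures is 60 × 0.05 + 40 × 0.26 = 13.4. Over all nine scenarios in 7.32 it runs from 90 × 0.05 + 10 × 0.44 = 8.9 to 60 × 0.15 + 40 × 0.42 = 25.8.

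**2. Inputs for the check.**
- N = 100; 40%, 20% or 10% detectable (7.32).
- SD 0.7 log10, correlation r = 0.4, effect 3 per log10 (7.31). The odds ratio is used as a hazard ratio.
- Plasma read every 8 weeks from week 16 to week 96, so 80 weeks.
- Overall later failure of 15% or 30%. The first lies within the 9% to 26% implied by 7.32. The second lies above it and equals the 7.31 rate at mean viral loads.
- Assumption: the baseline correlation and the effect size hold in subjects suppressed at week 16.

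**3. Closed form, 40% detectable.** Detectable means the top 40% of a standard normal nonblood score, so the cut is at 0.253, where the normal density is 0.386.
- Difference in mean score between groups: 0.386/0.4 + 0.386/0.6 = 1.61.
- Difference in mean baseline blood viral load: 1.61 × 0.4 × 0.7 = 0.451 log10.
- Apparent log hazard ratio with no nonblood effect: 0.451 × ln 3 = 0.495, that is a hazard ratio of about 1.64.
- Log-rank rejection is about Φ(0.495 × √(D × 0.4 × 0.6) − 1.96) for D failures. With D = 30 this is Φ(−0.63) = 26%. With D = 15 it is Φ(−1.02) = 15%.

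**4. Simulation.** Time to failure is exponential with rate λ·exp(ln 3 × x), where x is centred log10 baseline blood viral load. There is no independent nonblood effect. 1,500 trials per setting, nominal 5%:

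| Detectable | Later failure | Log-rank rejects | Cox with baseline blood rejects |
|---|---|---|---|
| 40% | 15% | 14.1% | 3.5% |
| 40% | 30% | 23.5% | 4.2% |
| 20% | 15% | 17.1% | 3.6% |
| 20% | 30% | 23.7% | 5.1% |
| 10% | 15% | 17.5% | 4.0% |
| 10% | 30% | 22.5% | 4.3% |

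In the second row the apparent failure rates are 25% and 37%. A separate set of runs with 15% to 25% failure gave 18% to 25% for log-rank and 4% to 6% for adjusted Cox.

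**5. Sensitivity to the borrowed values** (40% detectable, 30% failure):

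| r | Hazard ratio per log10 | Log-rank | Adjusted Cox |
|---|---|---|---|
| 0 | 3 | 4.5% | 4.2% |
| 0.2 | 3 | 9.5% | 5.4% |
| 0.6 | 3 | 46.7% | 5.5% |
| 0.4 | 2 | 13.9% | 3.8% |
| 0.4 | 1.5 | 8.6% | 4.3% |

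Other runs gave 11% at r = 0.4 with hazard ratio 2, and 8% at r = 0.2.

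**6. Does the week 16 restriction solve it?** Suppression was modelled explicitly: 70% suppressed at mean viral load, odds ratio 1/3 per log10 (both assumed), 20% later failure, N = 100, 1,000 trials per setting. Log-rank still rejected in 15% to 18% at r = 0.4 with hazard ratio 3, against about 6% for adjusted Cox. It rejected in 10% to 11% at hazard ratio 2, and in about 6% at r = 0.2 with hazard ratio 2.

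**The case against.** **The objectives differ.** Objective 2.11 names blood and nonblood viral load. Objective 2.12 names only nonblood viral load and asks for its relationship with later failure, in a study that calls itself exploratory. An unadjusted association is a legitimate answer to that question and is useful for identifying who will fail. This stands: the log-rank test is valid for marginal association. A reader might infer from the tables that the planned test has a type I error of 14% to 25%. It does not. In these simulations a marginal association truly exists, and the rates apply to the hypothesis of independent prediction.

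**The inputs are borrowed.** The 0.4 comes from baseline blood and seminal plasma. The odds ratio of 3 belongs to the objective 1 endpoint, which includes failures at week 16. The documents give neither value for suppressed subjects, nor any correlation for saliva or lymphoid tissue. The Background says that genital HIV-1 DNA correlates poorly with plasma RNA, so the premise is weak for that measure. This too stands, and it leaves the size uncertain.

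**Residual viraemia.** A reader might infer that week 16 plasma of 50-199 copies/mL is a demonstrated second confounder that must enter the model. The documents give no prevalence, failure rate or detection rate by that split. Results taken from a coenrolled study need not come from the 50-copy assay.

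**Few events.** With about 9, 11 and 13 failures (the 5% scenarios at 10%, 20% and 40% detectable), a three-term Cox model produced near-separation, meaning a coefficient above 5 in absolute value, in 29%, 13% and 7% of null trials. That argues against a compulsory second covariate. It does not argue against one covariate already used in 7.51.

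**An analysis plan may name Cox covariates.** It may, but 7.52 itself decides which analysis is committed and which is optional.

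**Conclusion.** The point holds as a limit on interpretation. As written, 7.52 can show that week 16 nonblood virus is associated with later failure. It cannot show that it predicts failure beyond baseline blood viral load, although the protocol assumes that blood viral load both predicts failure and correlates with nonblood viral load.

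If the 7.31 planning values applied to suppressed subjects, a log-rank result would be mistaken for independent prediction in roughly 14% to 25% of trials. With a weaker correlation (0.2) or hazard ratio (1.5 to 2) the figure is mostly about 8% to 14%, and lower if both are weak. With no correlation it is 5%. The adjusted Cox model stays near 5% throughout. The direction is well supported. The size rests on carrying over the correlation and on using an odds ratio as a hazard ratio.

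The documents do not support a stronger conclusion that the planned test is invalid or that the objective fails. This is an inexpensive improvement.

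**What to change.** In 7.52, commit to testing the nonblood term in a Cox model that includes baseline log10 plasma HIV-1 RNA, as 7.51 does. Keep the Kaplan-Meier curves and the log-rank test as the unadjusted companion. Add week 16 plasma level (below 50 versus 50-199 copies/mL) only as a sensitivity analysis, if the number of failures permits.

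The cost is a sentence or two. Baseline plasma viral load is already collected, and section 7.5 defines it as the mean of the preentry and entry log10 values. The statistical price is one degree of freedom and somewhat less stable estimates when failures are few.
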